**Figure 5 figure5:**
[figure not shown]
Procedures for the Risks, Attitudes, Norms, Abilities, and Self-regulation (RANAS)–based SMS text messaging intervention for smallholder farmers in Uganda. KAP: knowledge, attitude, and practice; PPE: personal protective equipment.

### Outcome Measures

#### Overview

The coprimary outcomes of the study are (1) pesticide KAP scores indicating performance along the educational curriculum and (2) PPE use (to cover all body parts). Secondary outcomes are the psychosocial determinants based on the RANAS framework regarding PPE use, frequency of using gloves when handling pesticides, algorithm-based pesticide EISs, and frequency of health signs and symptoms associated with pesticide poisoning. All measures were self-reported. The full questionnaire, programmed to be used in Open Data Kit (ODK; Get ODK Inc), can be found in Multimedia Appendix 5. Items using Likert scales had 5 answer options and were augmented with a visual 5-dot scale to increase participants’ understanding, as has been shown to be helpful in other studies to support responding populations with low literacy [26]. The outcomes are summarized in Textbox 1.

Summary of the objectives and outcomes of the study.
**Objective 1: knowledge, attitude, and practice on pesticide handling**
Knowledge mean scoresAttitude mean scoresPractice mean scores
**Objective 2: pesticide exposure**
Personal protective equipment (PPE) use exposure scoresChange scoresChanging cloths (CHANGE) exposure scoresExposure intensity scores (EIS)Yearly pesticide application daysYearly pesticide exposure (EIS^Year^)
**Objective 3: health signs and symptoms associated with pesticide poisoning**
Sum of health signs and symptomsCategory of symptoms (low and high based on the baseline median)
**Objective 4: effect on PPE use**
Mean frequency of using 8 PPE items to cover the whole body [23,34]Mean frequency of using gloves [23,34]
**Objective 4: determinants of behavior change regarding PPE use**
Mean score of the following [29,35]:Intention to buy PPEIntention to use PPEVulnerabilitySeverityResponse efficacyAttitude: costsAttitude: fitting clothesAttitude: time consumingFeeling: uncomfortableFeeling: proudFeeling: weakOverall rate of benefitDescriptive norm (others’ behavior)Injunctive norm (others’ approval)Personal normAction knowledgeConfidenceAction plan to buy PPEAction plan to wear PPEBarrier planningEffortCommitment

#### KAP Assessment

##### Overview

KAP scores were assessed based on 16 items grouped around a similar training module separately for KAP (the full list of questions can be found in Multimedia Appendix 6). The KAP items were developed based on previous KAP assessments in the Pesticide Use in Tropical Settings survey [21] and another study [36] and adapted to assess KAP for 4 out of the 5 modules of the educational intervention curriculum on pesticide handling. The fifth module on IPM was not considered for the KAP scores as it was mainly related to pesticide product use and is captured in the exposure frequency under objective 2.

##### Example KAP Scoring

Knowledge questions were binary (eg, “The name of the plant protection product active ingredients can be found on the label of the product” [*true*, *false*, or *not sure*]). For every correct answer, 1 point was added to the knowledge score, resulting in final scores ranging between 0 and 16. The higher the score, the more knowledge the farmer had on safe pesticide handling. The “Not sure” responses were treated as “False.”

Attitude was measured using a 5-point Likert scale (eg, “It is important for me to know the active ingredients in a given plant protection product” [*agree not at all*=1; *agree a little*=2; *somewhat agree*=3; *rather agree*=4; *strongly agree*=5; *do not have an opinion*=coded as missing]).

Practice was also measured using a 5-point Likert scale (eg, “I look for the name of the active ingredients when buying or using a given pesticide product” [*never*, 0%=1; *rarely*, 25%=2; *sometimes*, 50%=3; *often*, 75%=4; *always*, 100%=5; *do not have an opinion*=coded as missing]).

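### The knowledge scoring sentence can be read as crediting 'not sure' as the answer 'false'; it should state that 'not sure' scores 0 on every item, whatever the item's key

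*Protocol article*

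**What the plan says.** The rule is in the protocol article under Outcome Measures, KAP Assessment, Example KAP Scoring. It opens with "Knowledge questions were binary", then gives an example item with three response options: true, false and not sure. Scoring is set as "For every correct answer, 1 point was added to the knowledge score, resulting in final scores ranging between 0 and 16". The score is interpreted as "The higher the score, the more knowledge the farmer had on safe pesticide handling". The paragraph ends with "The “Not sure” responses were treated as “False".

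The KAP overview gives the item count: "KAP scores were assessed based on 16 items grouped around a similar training module separately for KAP". It refers the full question list to Multimedia Appendix 6, which is not part of the text at hand. The one knowledge item shown is "The name of the plant protection product active ingredients can be found on the label of the product"; its correct answer is not stated, but it reads as true.

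The Outcome Measures overview makes the KAP scores coprimary together with PPE use, and Textbox 1 lists knowledge as one of the three scores under objective 1.

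**The concern.** The closing sentence allows two codings, and they differ on any item whose correct answer is 'false'.

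- Reading A: 'False' means 'incorrect'. 'Not sure' earns 0 on every item.
- Reading B: 'False' means the response option. 'Not sure' is recoded to the answer 'false', earning 0 on true-keyed items and 1 on false-keyed items.

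Reading B is the literal one. Earlier in the paragraph 'false' occurs only as a response label, and the closing sentence puts 'Not sure' and 'False' in the same quotation marks and capitals. Calling three-option items binary also fits a recode to true/false. Under B, credit for not knowing depends on how the item happens to be worded, and the score no longer orders farmers by knowledge. If the share answering 'not sure' differs between arms, the knowledge comparison is distorted as well.

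**Working it through.** **Inputs from the article.** 16 items; 1 point per correct answer; three response options; 'not sure' treated as 'False'.

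**Not in the article, so assumed below.** K, the number of false-keyed items (possible range 0 to 16), and the shares of correct and 'not sure' answers in each arm.

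**Step 1, the stated range.** 16 items × 1 point gives 0 to 16, as the article says. This holds under both readings, so it does not show which was used.

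**Step 2, the farmer who answers 'not sure' throughout.** Reading A gives 0. Reading B gives K. For any K above 0, B credits a farmer who has shown no knowledge. This needs no assumed rates.

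**Step 3, the between-arm difference.** Let c be the share correct and u the share 'not sure' at follow-up, with T for trained and C for control.

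- True-keyed item, A or B: effect = c_T − c_C.
- False-keyed item, A: effect = c_T − c_C.
- False-keyed item, B: effect = (c_T + u_T) − (c_C + u_C).

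Summing over items: effect under B − effect under A = K × (u_T − u_C), where u is the mean 'not sure' share on the false-keyed items. This is for the raw difference in follow-up means; an adjusted model would alter it somewhat.

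**Step 4, size under assumed shares.** With u_C = 0.30 and u_T = 0.10:

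- K = 2: 2 × (−0.20) = −0.4 points
- K = 4: 4 × (−0.20) = −0.8 points
- K = 8: 8 × (−0.20) = −1.6 points

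Other assumed pairs over the same K: 0.20 versus 0.05 gives −0.3 to −1.2; 0.40 versus 0.20 gives −0.4 to −1.6.

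**Step 5, relative to the effect under A.** Effect under A = 16 × (c_T − c_C). All shares are assumed and taken as the same for every item.

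| Correct, C to T | 'Not sure', C to T | Effect under A | Effect under B, K = 4 (B/A) | Effect under B, K = 8 (B/A) |
|---|---|---|---|---|
| 0.50 to 0.75 | 0.30 to 0.10 | 4.00 | 3.20 (0.80) | 2.40 (0.60) |
| 0.60 to 0.75 | 0.20 to 0.10 | 2.40 | 2.00 (0.83) | 1.60 (0.67) |
| 0.70 to 0.80 | 0.10 to 0.05 | 1.60 | 1.40 (0.88) | 1.20 (0.75) |
| 0.50 to 0.65 | 0.20 to 0.20 | 2.40 | 2.40 (1.00) | 2.40 (1.00) |
| 0.50 to 0.65 | 0.10 to 0.20 | 2.40 | 2.80 (1.17) | 3.20 (1.33) |

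With K = 0 the ratio is 1.00 in every row. The last two rows show that the direction is not fixed: equal shares give no bias, and a rise in 'not sure' enlarges the effect.

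**The case against.** The best defence is that 'False' simply means 'incorrect'. The article awards points only for correct answers and says that a higher score means more knowledge. Within that sequence, the last sentence can be taken as explaining how a third option fits a right/wrong score. The literal reading would contradict the sentence just before it. The only item shown reads as true-keyed, and for such an item both readings give 0. No false-keyed item appears in the text at hand, the section is headed as an example, and the full list is in an appendix.

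Much of this stands. A reader might infer that the trial did award points for not knowing and that the knowledge effect is therefore biased toward no effect. The documents do not support that. They do not show that the literal recode was used, that any item is false-keyed, or that training lowers the 'not sure' share. A fall in 'not sure' after a 2-day workshop is plausible, but no such rates are reported. The article also gives no SD or target difference for the knowledge score, so the importance of 0.4 to 1.6 points cannot be judged.

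The defence does not rescue the sentence. If 'incorrect' was meant, the wording names a response option instead and an analyst could code it that way. Nor is this a detail left to an analysis plan: the article states the scoring rule itself, in words that permit an invalid coding.

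**Conclusion.** The point holds as a badly fixed scoring rule, not as a demonstrated bias. Taken literally, the sentence contradicts the article's own interpretation of the score on any false-keyed item; taken charitably, it misstates the rule.

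Any distortion of the between-arm difference equals K × (u_T − u_C). It is zero if K = 0, if the 'not sure' shares are equal between arms, or if 'False' meant 'incorrect'. If training lowers 'not sure', the effect shrinks, by 0.4 to 1.6 points of 16 for K = 2 to 8 at assumed shares of 30% versus 10%. If training raises 'not sure', the effect grows.

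Only the knowledge part of the KAP coprimary outcome is exposed. The attitude and practice scores use Likert scales with a different rule, and PPE use and the exposure score behind the sample size do not involve these items. The sentence should be corrected, because it governs part of a coprimary outcome and correcting it costs almost nothing.

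**What to change.** Replace the sentence with: 'Not sure is scored 0 (not correct) on every knowledge item, whatever the item key.' Apply that rule to the raw three-option responses at both baseline and follow-up. Check the scoring code, and if 'not sure' was recoded to the answer 'false', rescore both time points before the knowledge analysis.

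The cost is one sentence and one line of code. 'Not sure' was a recorded option, so no new data are needed provided the raw responses were kept.

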#### Pesticide Exposure

The pesticide EIS (ranging from 0 to 13) during an average application day was based on a semiquantitative exposure algorithm specifically modified [23], applied, and validated for smallholder farmers who use handheld knapsack sprayers in LMICs as described in recent studies [37-39]. Concisely, EIS estimates are derived from a comprehensive evaluation involving 5 key factors. These factors are (1) mixing pesticides (MIX; score of 5); (2) the application of pesticides using a knapsack (APPLICATION; score of 8); (3) the type of PPE used, protecting different body parts, and accounting for differences in application frequency (PPE; score of 0.14-1); (4) the time taken to change clothing after pesticide handling (CHANGE; score of 0.7-1); and (5) the postapplication bathing routine (SHOWER; score of 0.7-1), as illustrated in equation 1. Mixing and application of pesticides are expected to increase exposure, whereas use of PPE, changing clothes, and showering after an application reduce exposure.

EIS = (MIX + APPLICATION) x PPE x CHANGE x SHOWER **(1)**

Yearly pesticide exposure was assessed using [23] (1) the yearly pesticide application days over the previous 12 months and (2) the EIS during an average application day, as indicated in equation 2. The pesticide application days were captured using a spreadsheet that included the pesticide products used by the farmer in the previous 12 months and the number of days each product was applied [39.

EIS^Year^ = EIS × Yearly pesticide application days **(2)**

#### Health Signs and Symptoms Associated With Acute Pesticide Poisoning

Farmers’ health was assessed using a checklist of 31 symptoms associated with acute poisoning (eg, dizziness, anxiousness, nausea, vomiting, sleeping difficulties, weakness of the limbs, and changes in taste and smell [40]). Participants were asked whether they presented the symptoms (yes or no) and, if they did, the frequency with which they experienced them (once a year, once a month, once a week, or more than once a week) and whether they experienced them after spraying pesticides. The sum of the symptoms experienced by the farmers after pesticide application will be calculated and further dichotomized based on the baseline median distribution of the signs and symptoms.

#### Frequency of PPE Use and its Psychosocial Determinants

Using PPE to cover all body parts was assessed using behavioral frequency measures as is common in behavioral science [34]. Participants were shown pictures of 15 PPE items to cover the whole body and were asked about the frequency of using these items in the previous 12 months, with answer options ranging from *always*=1 to *never*=5. These items were reverse coded as infrequent use (1) and frequent use (5) and categorized into 8 means for the covered body parts: “eyes, mouth, hands, arms, legs, feet, trunk, and head” [23]. To create the total frequency of PPE use to cover all body parts, a sum of all categories’ means was calculated (ie, frequency of PPE use = mean [frequency of using items to cover the hands] + mean [frequency of using items to cover the mouth] + ... + mean [frequency of using items to cover the feet).

Frequency of using gloves*.* In addition, as the hands are the most exposed body part during pesticide handling [23], we assessed the mean frequency of using PPE to cover the hands through common behavioral frequency assessment [34]. Participants were asked about the frequency of using PPE to cover their hands (using any kind of gloves).

Exposure modified by PPE use was assessed using the modifying PPE variable from the pesticide exposure scores [23]. This can account for the material of the PPE being used and the exposure risk of different body parts. For example, the hands account for 40% of pesticide exposure, whereas the eyes-only account for 10% of exposure.

Psychosocial determinants of PPE use (RANAS factors) were assessed using the measurements proposed by the RANAS model [29,35]. All items were pretested in an unpublished pilot study in Uganda. The items assessed the 17 psychosocial determinants proposed by the RANAS approach asking participants how much they agreed with certain RANAS-based questions (see Table 1 in the *Description of the Interventions* section for sample items) using a 5-point Likert scale (*not at all*=1; *very much*=5). For each scale, multiple items were averaged. Beliefs about cost benefits in the attitude category were assessed using single rather than averaged items given their low internal consistency at baseline.

Sociodemographic characteristics included age, educational level, marital status, number of children, smoking status, drug and alcohol use, main occupation, and monthly income. Farming characteristics included farm size, main farming objective, number of farm workers, major crops grown, main pest management practices, debut age for working on farms, age when they started mixing and applying pesticides, who mixes the pesticides, disposal of pesticide containers, who washes the pesticide application equipment, field re-entry after pesticide application, sources of farming and pesticide use information, training in pesticide use, knowledge of routes of exposure, and negative consequences of pesticide use.

### Data Collection and Management

The study data were collected using an electronic questionnaire developed using ODK. The research assistants were trained before the baseline interviews on the objectives of the study, ethical aspects, and the use of the ODK. They collected pretest data in a pilot study from 20 smallholder farmers from another district that was not part of our study. The research assistants visited the farmers either in their homes or on the fields and administered the computer-assisted interviews in either 3 local dialects (Luganda, Runyankore, or Ateso) or English. At the end of each day, the data were uploaded to a secure server. A data quality management team inspected the data regularly for any inconsistencies or errors, and where found, the responsible research assistants were contacted, and appropriate resolutions were reached. The data were securely stored in a password-protected database with restricted access.

### Statistical Analyses

Statistical analyses will be conducted using Stata (version 15; StataCorp) and R (version 4.3.1; The R Foundation). The outcomes will be based on intention-to-treat analyses, and missing data values will be computed using the multivariate imputation chained equations R package. The effect of the interventions on the 3 arms will be analyzed using the intervention arms as dummy-coded predictors and the follow-up measures as outcomes in multivariate mixed models with the cluster (subcounty) as the random effect. Sensitivity analyses are planned to control for differences in sex, age, educational level, previous training, and annual pesticide use days. For objective 2, subanalyses of factor scores (type of PPE, time taken to change clothing after pesticide handling, postapplication bathing routine, mixing pesticides, and application of pesticides using a knapsack) used to compute the exposure algorithms will be made to test their variation resulting from the interventions.

Intervention effects on KAP, PPE use (frequency of using PPE for all body parts, frequency of using gloves, and exposure modified by pesticide use), algorithm-based pesticide EIS, and health signs and symptoms associated with acute pesticide poisoning will be analyzed in a model testing the control group (0) against the educational intervention (1) and against the educational intervention+RANAS-based SMS text messages (1). For the intervention effects on PPE and glove use (objective 4), all arms will be compared by testing the educational intervention against the educational intervention+RANAS-based SMS text messages (0) in an additional model.

To understand the psychosocial mechanisms of the interventions (objective 5), we will perform 2 mediation models with multiple psychosocial behavioral determinants as mediators, one testing the educational intervention group (1) against the control group (0) and one testing the educational intervention+RANAS-based text message group (1) against the educational intervention (0). The mediation analyses will use the change scores (follow-up value – baseline value) for all RANAS-based psychosocial determinants as mediators and PPE use as the outcome, operationalized as the frequency of using PPE to cover all body parts and using gloves.

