**Methods:**

We enrolled 539 Ugandan smallholder farmers in 12 clusters (subcounties). The clusters, each with 45 farmers, were randomly allocated to one of the three arms: (1) educational intervention, (2) educational intervention+RANAS-based SMS text messages, or (3) control group. The educational intervention comprised a 2-day workshop that targeted multiple aspects of safe pesticide handling, whereas the SMS text messages targeted the use of personal protective equipment (PPE) and were based on the RANAS approach. For intervention development in this study, this approach includes identifying psychosocial determinants of PPE use at baseline and selecting behavior change techniques to target them in SMS text messages. The primary outcomes of the study are (1) pesticide knowledge, attitude, and practice scores indicating performance throughout the educational intervention; and (2) frequency of PPE use. Secondary outcomes are the RANAS-based behavioral determinants of PPE use, the frequency of glove use, algorithm-based pesticide exposure intensity scores, and signs and symptoms of pesticide poisoning. The outcomes were assessed in structured interviews before the intervention (baseline) and at the 12-month follow-up. The effect of the interventions among the arms will be analyzed using the intervention arms and baseline measures as predictors and the follow-up measures as outcomes in linear multivariable mixed models including the clusters as random effects. The mediating psychosocial determinants of the interventions will be assessed in multiple mediation models.

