### Randomization and Blinding

After the baseline survey in October 2020, a total of 4 clusters each with 45 farmers were randomly assigned to one of the three arms, comprising 180 farmers per arm (Figure 1): (1) educational intervention, (2) educational intervention+RANAS-based SMS text messages, or (3) control group. One of the Swiss investigators who had no previous knowledge of the subcounties used Microsoft Excel (Microsoft Corp) random numbers to randomize the clusters to the arms. The allocation of the clusters was concealed from the participants. The participants were also blinded with regard to which arm other farmers had been assigned to. The investigators and facilitators knew which arm the farmers had been assigned to, and at the follow-up interviews, the research assistants could know which arm the farmers had been assigned to.

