### Sample Size Calculation

We estimated a sample size of 540 farmers that assumed a statistical power of 80% based on the estimated observed differences between the EISs of an average pesticide application between smallholder farmers who received training in pesticide handling and those who did not receive it in a recent survey in Uganda [23]. The trained group had a mean EIS of 0.47 (SD 0.10), and the untrained group had a mean EIS of 0.55 (SD 0.18). We assumed that the 2 planned intervention arms would show a similar effect distribution. Hence, we based our sample size calculation on the 2-sample means test assuming a cluster-randomized design, a total of 12 clusters equally distributed between the control and intervention groups, and an intraclass correlation coefficient of 0.4. The package *power two means* in the statistical software Stata (version 15; StataCorp) resulted in a cluster size of 40 farmers and a total of 480 farmers, which would reach a power of 80% at a significance level of 5%. To account for a possible dropout rate of 13% at follow-up based on a previous study in a similar setting [23], in each cluster, an additional 5 farmers were enrolled, hence constituting a total sample size of 540.

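### The Abstract's effect model includes baseline measures but the Statistical Analyses section's model does not, so the primary model for the coprimary outcomes is not fixed

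*Protocol article*

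**What the plan says.** The Abstract (Methods) states that intervention effects will be analysed "using the intervention arms and baseline measures as predictors and the follow-up measures as outcomes in linear multivariable mixed models", with the clusters as random effects.

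The Statistical Analyses section describes the effect model again as "using the intervention arms as dummy-coded predictors and the follow-up measures as outcomes in multivariate mixed models", with subcounty as the random effect. No baseline measure is named. The next sentence adds only this: "Sensitivity analyses are planned to control for differences in sex, age, educational level, previous training, and annual pesticide use days". The baseline value of the outcome is not in that list.

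Baseline values appear later in the section in one place only, the mediation models for objective 5: "The mediation analyses will use the change scores (follow-up value – baseline value) for all RANAS-based psychosocial determinants as mediators". That concerns the mediators. PPE use enters those models simply as the outcome.

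On the design, Randomization and Blinding says that "a total of 4 clusters each with 45 farmers were randomly assigned to one of the three arms", after the baseline survey, using Excel "random numbers to randomize the clusters to the arms". No stratification or balancing is described. The Sample Size Calculation, which is for the exposure intensity score (EIS), assumes "a total of 12 clusters equally distributed between the control and intervention groups, and an intraclass correlation coefficient of 0.4".

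**The concern.** The two sentences are otherwise nearly the same, but one has the baseline term and the other does not. For a continuous outcome measured before and after the intervention, that term decides whether the primary estimate compares follow-up means or baseline-adjusted follow-up means. The coprimaries are the knowledge, attitude and practice (KAP) scores and the frequency of PPE use.

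Three things are at stake.

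- **The primary model is open.** Follow-up ended in October 2021 and the investigators knew the allocation. With two models in print, either result could be presented as the planned one.
- **Imbalance.** Only 4 subcounties per arm are compared, so the arms can differ noticeably at baseline by chance. The arm-only model does nothing about the particular imbalance that occurred.
- **Precision.** The outcomes were already measured at baseline, so adjustment needs no new data.

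A smaller point concerns the sensitivity covariates. Annual pesticide use days is listed without a time point, while the outcome textbox makes yearly application days an objective 2 outcome. The list should say which measurement is meant.

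**Working it through.** The article gives no figure for the effect of baseline adjustment, so there is none to reproduce. The steps below size the consequence.

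**1. Inputs.** From the article: 4 clusters of 45 per arm at baseline; 494 farmers at follow-up, or 494/12 = about 41 per cluster; ICC 0.4, for EIS; EIS means 0.47 (SD 0.10) and 0.55 (SD 0.18). Not given, and therefore assumed over a range: the ICC of the coprimaries (0.05 to 0.4), and the baseline to follow-up correlation at cluster level (rc, 0.3 to 0.7) and individual level (ri, 0.3 to 0.5).

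**2. How far the ICC of 0.4 can be relied on.** Its source calculation does not return the stated 80% power. With 6 v 6 clusters of 40, the design effect is 1 + 39 × 0.4 = 16.6 and the effective n per group is 240/16.6 = 14.5. The SE is sqrt((0.10² + 0.18²)/14.5) = 0.054, so z = 0.08/0.054 = 1.48 and the two-sided power is about 31.5%. An ICC near 0.09 would give 80%. That is a separate matter, but it is a reason to treat 0.4 as the top of a range and not as the headline.

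**3. Chance baseline gap between two arms,** in outcome SD: sqrt(2 × (ICC + (1 − ICC)/45)/4).

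| ICC | ICC + (1 − ICC)/45 | SD of gap | 95% range |
|---|---|---|---|
| 0.05 | 0.0711 | 0.19 | ±0.37 |
| 0.1 | 0.1200 | 0.24 | ±0.48 |
| 0.4 | 0.4133 | 0.45 | ±0.89 |

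For scale, the planned EIS difference is 0.08/sqrt((0.10² + 0.18²)/2) = 0.08/0.146 = 0.55 SD. EIS is a secondary outcome, so this is not a benchmark for KAP or PPE use. Only the part of the gap that persists to follow-up enters the arm-only estimate.

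**4. Precision if the slope were known.** SE ratio = sqrt([ICC(1 − rc²) + (1 − ICC)(1 − ri²)/41] / [ICC + (1 − ICC)/41]). This gives 0.866 for rc = ri = 0.5, and 0.77 (ICC 0.05) to 0.72 (ICC 0.4) for rc = 0.7, ri = 0.5.

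**5. Precision when a cluster-level slope must be estimated.** With 12 clusters and 3 arms, a cluster-mean covariate takes the between-cluster degrees of freedom from 9 to 8, and the critical t from 2.26 to 2.31 (a factor of 1.02). It also inflates the variance by about 1 + 1/7 (a factor of 1.07 on the SE). Together this is about 1.02 × 1.07 = 1.09, which offsets part of the gain. Simulating the mean 95% interval width from a cluster-level analysis (41 per cluster, ICC 0.05 to 0.4) gives:

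| rc | ri | Change in interval width |
|---|---|---|
| 0.3 | 0.3 to 0.5 | 1-3% wider |
| 0.5 | 0.5 | 6-7% narrower |
| 0.7 | 0.5 | 17-23% narrower |

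**6. The individual baseline value alone.** Its slope comes mostly from within-subcounty data on several hundred farmers, so little of the cost in step 5 applies. As an approximation, take equal variances at both times and a slope b = 0.5. The between-cluster variance is then multiplied by 1 + b² − 2 × b × rc, which is 0.95, 0.75 and 0.55 for rc = 0.3, 0.5 and 0.7. The within-cluster part is multiplied by 1 − 0.25 = 0.75.

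**The case against.** The strongest reply is that the Statistical Analyses section never calls its model unadjusted and excludes no covariate. The Abstract positively states the adjusted model, and a condensed article may simply have dropped a term. That may be what happened. It does not settle the matter, because the fuller section lacks a term that the shorter one has, although it gives the arm coding, the random effect, the imputation package and five sensitivity covariates. It cannot be inferred that the investigators decided against baseline adjustment; all that follows is that the text does not fix the model.

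The rest of the reply limits the size of the point, and it stands. A reader might infer that the arm-only analysis is biased or invalid. It is not: randomization makes the estimator unbiased, and the subcounty random effect carries between-cluster variation into the SE. A reader might also infer that the imbalance is bound to be large, since 0.45 SD is close to the 0.55 SD planning effect. Both numbers belong to EIS, and at ICC 0.05 the gap SD is 0.19. Finally, a reader might take the SE cuts implied by step 4, 13% and 23-28%, as the gain on offer. They treat the slope as known, and a cluster-mean term estimated from 12 subcounties does not deliver them. At low correlation it costs a little precision.

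The article also does not say that follow-up use days will be the covariate; it gives no time point.

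**Conclusion.** The point holds as an inconsistency about the primary model, with a modest to material effect on precision. The Abstract and the Statistical Analyses section state different models for KAP and PPE use, and no listed sensitivity analysis supplies the missing term. This part rests on the text alone.

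The size rests on assumptions. The chance baseline gap has an SD of 0.19 to 0.45 outcome SD for ICCs of 0.05 to 0.4. For a cluster-level adjustment, the change in the 95% interval runs from 1-3% wider to 17-23% narrower as the cluster-level correlation goes from 0.3 to 0.7. Neither the ICC nor the correlation is given for the coprimaries. The consequences are imprecision, unadjusted imbalance in the one allocation that occurred, and a choice of model left open. An invalid test is not among them.

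**What to change.** In the Statistical Analyses section, state one primary model that matches the Abstract: the follow-up outcome on the two arm dummies and the individual baseline value of the same outcome, with a subcounty random intercept. Apply it to KAP, PPE use, glove use, EIS and the symptom sum, and keep the unadjusted model as a sensitivity analysis. A cluster-mean baseline term is optional, given its cost with 12 clusters. The dichotomized symptom outcome needs the logistic equivalent.

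In the list of sensitivity covariates, say that annual pesticide use days is the baseline value, because yearly application days is itself an objective 2 outcome.

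The cost is two or three sentences. The baseline data are already collected, and no figure elsewhere in the article changes.
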